### Sample size

For the sample size calculation, we assume that a difference between either EMA group and the control group within the margin −0.25< Cohen’s d <0.25 is clinically negligible. Therefore, a difference between groups of d = 0.25 should reach statistical significance in our analysis. We ran a power calculation in G*Power [27] for a repeated-measures analysis of variance (ANOVA), which is essentially the same analysis as linear mixed modelling when there are no missing values. A total number of 120 participants (40 per group) is required in order to obtain d = 0.25 with three assessment waves, a targeted power of .85, a significance level alpha of .05, and conservative estimations of correlations between measurements (*r* = .65) and variances of the differences between groups (non-sphericity correction epsilon = .8). Expecting 25 % drop-out at T12, we will recruit 160 participants. All participants will be included in the linear mixed model, which is robust for missing data.

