**Methods:**

This study is a 12-week randomised controlled trial comprising three groups: group 1 carries out EMA of mood and completes a retrospective questionnaire, group 2 carries out EMA of how energetic they feel and completes a retrospective questionnaire, group 3 is the control group, which completes only the retrospective questionnaire. The retrospective questionnaire (Centre for Epidemiologic Studies Depression scale; CES-D) assesses depressive symptoms and is administered at baseline, 6 weeks after baseline and 12 weeks after baseline. We aim to recruit 160 participants who experience mild to moderate depressive symptoms, defined as a Patient Health Questionnaire (PHQ-9) score of 5 to 15. This study is powered to detect a small between-groups effect, where no clinically relevant effect is defined as the effect size margin −0.25< d <0.25.

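### On the plan's own inputs an EMA-versus-control difference of d = 0.25 would usually not be significant, so significance cannot separate negligible from relevant reactivity at the ±0.25 margin

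*Protocol article*

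**What the plan says.** The Sample size section of the protocol article assumes that "a difference between either EMA group and the control group within the margin −0.25< Cohen’s d <0.25 is clinically negligible". It goes on: "Therefore, a difference between groups of d = 0.25 should reach statistical significance in our analysis". The Methods paragraph of the abstract uses the same margin as a definition: "no clinically relevant effect is defined as the effect size margin −0.25< d <0.25". The Discussion says that the mixed model can show effects larger than 0.25 in either direction, and that the design can detect both 6-week and 12-week effects.

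The calculation behind this is a repeated-measures ANOVA in G*Power: "A total number of 120 participants (40 per group) is required in order to obtain d = 0.25 with three assessment waves", with "a targeted power of .85, a significance level alpha of .05", a correlation of .65 between measurements and "non-sphericity correction epsilon = .8". Allowing for 25% drop-out, 160 are recruited, 1:1:1.

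Under Analyses, the primary model regresses T6 and T12 CES-D on baseline CES-D, group, time and their interaction. Estimates and confidence intervals are to be divided by the pooled SD, and the family-wise two-tailed level is .05 by Holm-Bonferroni. No rule compares those intervals with ±0.25.

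**The concern.** The margin is meant to mark where reactivity starts to matter, and the Sample size section ties it to significance: a difference at the margin is expected to come out significant. If that were true, the difference test would sort effects roughly into relevant and negligible. If it is false, a non-significant result is common even when the true effect lies on the boundary, and it says little about which side of ±0.25 the effect is on.

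This matters because the null answer is of practical interest. The Implications section says that an effect would limit EMA as an instrument, with immediate interest for projects already using it over long periods. A reader given a non-significant result, a stated power of .85 and a definition of no clinically relevant effect could easily conclude that such use is free of relevant reactivity.

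**Working it through.** **1. The plan's own figure.** The article does not name the G*Power test. The within-between interaction with k = 3 groups, m = 3 waves and f = d/2 = 0.125 reproduces it:

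- λ = N f² m ε / (1 − r) = 120 × 0.015625 × 3 × 0.8 / 0.35 = 12.86
- df = (k − 1)(m − 1)ε = 3.2 and (N − k)(m − 1)ε = 187.2
- Power = .851, and 120 / 0.75 = 160.

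The between-groups test on the same inputs has power of only .26. So 120 is right for an omnibus group-by-time interaction with f = 0.125.

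**2. What f = 0.125 means here.** Suppose both EMA groups differ from control by d = 0.25 at T6 and T12 and not at baseline. The interaction variance is the variance of (0, 1, 1) times that of (0, 0.25, 0.25): 0.2222 × 0.01389 = 0.00309, so f = 0.056. Then λ = 120 × 0.00309 × 3 × 0.8 / 0.35 = 2.54 and power is .23. The .85 does not carry over to the difference that the text describes.

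**3. The pairwise contrast.** For one EMA group versus control on the d scale, with equal SDs and r = .65 between all waves:

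- SE = √(v × 2/n)
- one time point, baseline-adjusted: v = 1 − r² = 0.5775
- mean of T6 and T12, baseline-adjusted: v = (1 + r)/2 − r² = 0.825 − 0.4225 = 0.4025
- n = 40 evaluable, or 53 if nobody drops out (160/3)

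Normal quantiles, before Holm:

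| Contrast | n per group | SE | p at observed d = 0.25 | 95% half-width | Power at true d = 0.25 |
|---|---|---|---|---|---|
| One time point | 40 | 0.170 | .14 | 0.333 | .31 |
| One time point | 53 | 0.148 | .09 | 0.289 | .40 |
| Mean T6/T12 | 40 | 0.142 | .08 | 0.278 | .42 |
| Mean T6/T12 | 53 | 0.123 | .043 | 0.242 | .53 |

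Example: 0.25/0.170 = 1.47, two-sided p = .14; 1.96 × 0.170 = 0.333. With t quantiles the half-widths at 40 per group are 0.338 and 0.282, so nothing changes. At the first Holm step for two comparisons (α = .025, multiplier 2.241) they are 0.381 and 0.318 by the normal approximation.

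**4. Detectable difference.** With 85% power at two-sided .05, it is (1.960 + 1.036) × SE. At 40 per group this is 2.996 × 0.170 = 0.51 at one time point and 2.996 × 0.142 = 0.43 for the mean. Keeping d = 0.25 would need 2v × 2.996² / 0.0625 per group: 166 and 116.

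**5. Showing negligibility.** The 90% interval must fit inside ±0.25 (two one-sided tests). At true d = 0 the chance is 2Φ(0.25/SE − 1.645) − 1, or 0 if that is negative:

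| Contrast | 40 per group | 53 per group |
|---|---|---|
| One time point | 0% (90% half-width 0.280) | 4% (0.243) |
| Mean T6/T12 | 9% (0.233) | 30% (0.203) |

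**The case against.** The strongest reply is that the article never says a non-significant result will be read as absence of relevant reactivity. The margin is introduced for the sample size calculation, the Implications section interprets only effects that are found, and confidence intervals on the d scale are already promised. This stands. A reader might infer that the authors intend to report p > .05 as negligible, but no sentence commits them to that. What remains is that the article defines no relevant effect by the margin, connects the margin to the result only through significance, and states that connection wrongly.

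A second reply is that, in a power paragraph, the sentence refers to a true d of 0.25, not an observed one. That is a fair reading, but the claim fails on it too: pairwise power is .31 to .42 at the planned evaluable number.

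A third is that a d of 0.25 can be significant. With all 53 per group retained and the T6/T12 effect averaged, p is about .043 with a half-width of 0.242, before Holm. So it would be too strong to say that d = 0.25 can never be significant or that every interval is wider than the margin. But the plan itself expects 25% drop-out and claims separate 6-week and 12-week detection. A correlation above .65, which the article calls conservative, would also help: at r = .75 and 40 per group the averaged half-width is about 0.245, while the single-time-point half-width is still about 0.26 at r = .80.

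Nor do the documents support resting the conclusion on the two EMA groups pooled. The margin is set for either EMA group. The pooled, averaged contrast at 80 versus 40 has SE 0.123, the same as one arm averaged at 53 per group, and shows equivalence only about 30% of the time at true d = 0.

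**Conclusion.** The statements in the Sample size section and the Discussion are wrong as written, on either reading of d = 0.25. The sample size arithmetic is not at fault: it is correct for the omnibus interaction entered, which is not the pairwise difference claimed. As a result, significance cannot separate effects inside ±0.25 from effects outside it, and equivalence is unlikely to be shown even if EMA has no effect at all.

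The size of the problem rests on r = .65 between all waves, equal SDs, baseline adjustment as planned, and 40 to 53 per group. A higher correlation or full retention softens it, most of all for the averaged contrast, but does not restore a power of .85 at the planned inputs. No planned test is invalid; the error lies in what the tests are said to show.

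**What to change.** 1. In Sample size, replace the sentence on d = 0.25 with what the pairwise comparisons deliver: at 40 evaluable per group and r = .65, before Holm, power of about .31 (one time point) or .42 (T6/T12 mean) for d = 0.25, or equivalently a detectable difference of about 0.51 or 0.43 at 85% power. Say that 120 refers to the omnibus interaction with f = 0.125. Correct the matching sentence in the Discussion.
2. State that a non-significant result is not evidence that the effect lies within the margin.
3. Prespecify a rule on the intervals already planned. For each EMA-versus-control contrast, reactivity is shown if the Holm-adjusted interval excludes 0. Clinically negligible is concluded only if the whole 90% interval for d lies within ±0.25. A result that meets neither is reported as inconclusive.
4. State the limits of that rule at true d = 0: about 0% to 4% for one arm at one time point and about 9% to 30% for one arm averaged over T6 and T12, at 40 to 53 per group.

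The pooled EMA-versus-control contrast may be reported as supplementary. The cost is wording and one decision rule, with no new data; the price is a less favourable stated power and more results labelled inconclusive.

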### Analyses

The primary outcome is the effect of EMA on depressive symptoms as measured by the CES-D at T6 and T12, comparing both EMA groups with the control group. To test this on all available data, we will conduct a mixed models repeated measures regression analysis, with T6 and T12 CES-D data as the dependent variable, and baseline CES-D scores, group (1, 2, 3), time (T6, T12) and the time*group interaction as independent variables. Effects will be expressed in terms of percentage of variance explained and Cohen’s d (by dividing raw regression parameter point estimates and confidence intervals by the pooled CES-D standard deviation).

For our secondary analysis, we will examine the EMA response rate over time, which gives an indication of response fatigue. Response fatigue will also be analysed by assessing response accuracy, here defined as a declining correlation over time between theoretically associated measures. Literature has shown that mood swings are associated with higher depressive symptoms [23]. Therefore, we will analyse the variance of the EMA and its correlation with the CES-D scores, taking into account the EMA ratings of the two weeks prior to the CES-D (i.e. weeks 5 and 6 for T6 and weeks 11 and 12 for T12). A decreasing variance of EMA ratings (i.e. increasingly stable responses) will result in a decreasing correlation coefficient (*r*) with the CES-D scores if the CES-D scores do not decrease. This might indicate a decline in validity.

We will maintain a family-wise two-tailed *p*-value of .05 using the Holm-Bonferroni method [24]. IBM SPSS Statistics 23 [25] and R [26] will be used for all analyses.

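### The sample size was computed for a three-wave repeated-measures ANOVA, but the planned mixed model has two outcome waves with baseline as covariate, so the stated 85% power at d = 0.25 does not apply to it

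*Protocol article*

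**What the plan says.** The Sample size section of the protocol article sets the target: "a difference between groups of d = 0.25 should reach statistical significance in our analysis". The comparison it has in mind is "a difference between either EMA group and the control group within the margin" of ±0.25. It then gives the result: "A total number of 120 participants (40 per group) is required in order to obtain d = 0.25 with three assessment waves", with "a targeted power of .85, a significance level alpha of .05", correlation .65 and non-sphericity correction .8. The calculation is for a "repeated-measures analysis of variance (ANOVA), which is essentially the same analysis as linear mixed modelling when there are no missing values". The section does not say whether the between, within or interaction effect was powered. Allowing for 25% drop-out at T12, 120 becomes 160.

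The Analyses section describes the model that will be fitted. It is a mixed model "with T6 and T12 CES-D data as the dependent variable". The predictors are baseline CES-D, "group (1, 2, 3), time (T6, T12) and the time*group interaction as independent variables". The stated aim is to compare both EMA groups with control at T6 and T12, with Holm-Bonferroni control at a family-wise two-tailed .05. The section does not say whether the primary test is per wave, averaged over waves or an omnibus test.

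The Abstract describes the study as powered for a small between-groups effect. The opening of the Discussion says the mixed model can show effects beyond d = 0.25 in either direction.

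**The concern.** The protocol makes the equivalence of the two analyses conditional only on there being no missing values. Missing data are not what separates them. The ANOVA that was sized has T0, T6 and T12 as outcome waves; the planned model has T6 and T12, with T0 moved to the covariate side. That move changes what each term means:

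- With T0 as an outcome, an EMA effect that arises after baseline shows up as group-by-time.
- With T0 as a covariate, the same effect shows up in the group contrasts. The time*group term then compares only the T6 effect with the T12 effect.

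A power figure computed for one term in the first model cannot be transferred to a different term in the second. At stake is the claim on which the trial relies: that a difference at the edge of the negligible range would reach significance. If power at that difference is well below 85%, a non-significant result says much less about absence of reactivity than the protocol implies.

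**Working it through.** **1. Reproducing the stated 120.** Inputs from the Sample size section: d = 0.25, so f = d/2 = .125; k = 3 groups; m = 3 waves; r = .65; epsilon = .8; alpha = .05. G*Power formula for the within-between interaction:

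- λ = f² · N · m · ε / (1 − r) = .015625 × 120 × 3 × .8 / .35 = 12.86
- df1 = (k − 1)(m − 1)ε = 3.2; df2 = (N − k)(m − 1)ε = 187.2
- Power = .851 at N = 120, and .841 at N = 117, the next smaller equal allocation.

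So 120 is the exact threshold for this test. Other settings do not give it:

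| Effect tested | N for 85% power |
|---|---|
| Between groups, f = .125, k = 3, m = 3 | 540 |
| Between groups, f = .25, k = 3, m = 3 | 138 |
| Within factor, f = .125, k = 3, m = 3 | 99 |
| Interaction, k = 2, m = 3 | 98 |
| Interaction, k = 3, m = 3, epsilon = 1 | 105 |
| Interaction, k = 3, two waves | 126 |

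Drop-out: 120 / (1 − .25) = 160, as stated.

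**2. The EMA effect in the planned model.** Assumptions: unit CES-D variance, correlation .65 between every pair of waves, complete data, and the same effect d = 0.25 at T6 and T12. Variance per person after adjusting for baseline:

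- Mean of T6 and T12: (1 + .65)/2 − .65² = .825 − .4225 = .4025
- One wave: 1 − .65² = .5775

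For one EMA-control contrast with n per group, SE = √(2 × variance / n) and the non-centrality is .25 / SE. For n = 40 the SE is √(2 × .4025/40) = .142 averaged (non-centrality 1.76) and √(2 × .5775/40) = .170 for one wave (non-centrality 1.47). For n = 53 the averaged SE is .123. Power uses the non-central t with 3n − 4 degrees of freedom:

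| Contrast | n per group | two-sided alpha | power at d = 0.25 |
|---|---|---|---|
| Averaged over T6 and T12 | 40 | .05 | .42 |
| Averaged over T6 and T12 | 40 | .025 | .31 |
| Single wave | 40 | .05 | .31 |
| Averaged over T6 and T12 | 53 (no drop-out) | .05 | .52 |

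Using only the two compared groups for the degrees of freedom (2n − 3) changes the first line to .41. The 2-df omnibus group test also gives .42 at 40 per group; simulation of that test (4000 runs) gave .415.

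**3. What the averaged contrast can detect or would need.** With 40 per group, 85% power at .05 needs d ≈ (1.98 + 1.04) × .142 = 0.43. For d = 0.25, the averaged contrast needs about 117 per group (351 in total) at .05 and 140 (420) at .025. A single wave needs 167 (501) at .05.

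**4. The time*group term in the planned model.** With a constant effect the T6-minus-T12 difference is the same in all groups, so the test rejects at alpha whatever the size of d. Simulation gave 4.7% at d = 0.25 and 5.4% at d = 0.5.

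**5. Would the three-wave analysis deliver the 85%?** Take the pattern 0, d, d in both EMA groups and 0, 0, 0 in control. The interaction effects have root mean square 2d/9 = .056, not .125. Under sphericity λ = 40 × (36/81) × .0625 / .35 = 3.17 on 4 and 234 df, which gives about 25% power. Reverting to the three-wave ANOVA would therefore not restore the stated figure for this pattern.

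**The case against.** Three points on the other side carry weight.

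- A reader might infer that the trial would miss a sustained EMA effect. The documents do not support that. The Analyses section defines the primary question as EMA groups versus control and includes group in the model; those contrasts estimate a constant effect. It never makes time*group the primary test. The rejection rate at alpha in step 4 is true by construction and matters only if someone reads time*group as the reactivity test.
- A reader might infer that the Sample size section itself adopts the interaction as the test of reactivity. It does not name a term, and it speaks of a difference between groups. The interaction is deduced from the exact match with 120; the deduction is strong, but it remains a deduction.
- The comparison, the time points and the multiplicity rule are given. Contrast coding and reference levels are commonly left to an analysis plan that is not shown here, so their absence is not a fault. Nor do the documents make an averaged contrast the only sound choice: the Background expects a short-term effect, and the Discussion wants separate 6-week and 12-week effects, which per-wave contrasts serve equally well.

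None of this rescues the two statements that are printed: that the analyses are in essence the same, and that d = 0.25 should be detected with 85% power. Both are wrong for the planned model, whichever EMA-control contrast is chosen.

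**Conclusion.** The point holds as a mismatch between the analysis that was sized and the analysis that is planned. For the EMA-versus-control comparison at d = 0.25, power is roughly .31 to .42 with 40 per group, depending on whether the contrast is per wave or averaged and on the Holm step. It is about .52 for the averaged contrast at .05 if all 53 per group stay. Participants who leave between T6 and T12 still contribute T6 data, so the averaged contrast at .05 should fall between .42 and .52 if drop-out is no worse than planned.

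These figures rest on compound symmetry with the protocol's r = .65, d on the raw CES-D standard deviation, an equal effect at both waves for the averaged contrast, and no missing data within each scenario. The protocol's epsilon of .8 allows for some departure from that structure, so the second decimal should not be over-read. The gap to .85 is too wide to be explained by it. The data and the model remain usable; what needs correcting is the power claim and its link to the primary test.

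**What to change.** - Sample size: delete the sentence equating the repeated-measures ANOVA with the mixed model. Restate the power at d = 0.25, or the detectable d, for the contrasts below, including the Holm step and the planned drop-out.
- Analyses: state the primary tests as EMA-mood minus control and EMA-energy minus control, estimated from the planned model, either averaged over T6 and T12 or at each wave with Holm across all the tests. Use time*group only to test whether the effect changes between T6 and T12.
- Abstract and opening of the Discussion: bring the statements about what the trial can detect into line with the restated figure.

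The cost is a few lines of text and no extra data. The stated power becomes less favourable. If the averaged contrast is chosen, some sensitivity is lost should the effect exist at T6 only; if per-wave contrasts are chosen, power per test is lower and the Holm family is larger.

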## Discussion

This study aims to investigate whether self-rated EMA of depressive symptoms could induce assessment reactivity among mildly depressed individuals. The linear mixed model analyses can show an effect of Cohen’s d >0.25 (and < −0.25) on retrospectively measured depressive symptoms between groups. The 12-week study period and repeated measures design enable us to detect both short-term (6 weeks) and longer-term (12 weeks) effects on retrospectively measured depressive symptoms, as well as response fatigue.

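### The stated 85% power for d = 0.25 is wrong: on the protocol's own inputs, 120 completers give about 23% to 42%, depending on the test

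*Protocol article*

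**What the plan says.** The Sample size section of the protocol article treats differences in CES-D inside ±0.25 SD between either EMA group and control as negligible. It concludes that "a difference between groups of d = 0.25 should reach statistical significance in our analysis". The number comes from a G*Power calculation "for a repeated-measures analysis of variance (ANOVA), which is essentially the same analysis as linear mixed modelling when there are no missing values", and the result is given as: "A total number of 120 participants (40 per group) is required in order to obtain d = 0.25 with three assessment waves". The other printed inputs are power .85, alpha .05, correlation .65 between measurements and a non-sphericity epsilon of .8. Allowing for 25% drop-out, 120/0.75 = 160 are to be recruited. That inflation is correct.

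The Analyses section fixes what d means: estimates are standardised "by dividing raw regression parameter point estimates and confidence intervals by the pooled CES-D standard deviation". So d is an ordinary standardised difference between groups. The planned model takes T6 and T12 as outcomes and baseline CES-D as a covariate, with group, time and their interaction. A family-wise two-tailed .05 is kept by Holm-Bonferroni.

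The claim recurs twice. The Abstract says "This study is powered to detect a small between-groups effect". The Discussion says "The linear mixed model analyses can show an effect of" more than 0.25 in either direction.

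**The concern.** Forty per group is very few for a 0.25 SD difference at 85% power, even with a correlated baseline. The article gives d as the target but used a repeated-measures ANOVA routine that works in Cohen's f, and it names neither the test chosen nor the f entered. A wrong conversion between the two scales would make the required sample look far too small.

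The stakes are in the interpretation. The protocol draws a line at ±0.25 between negligible and relevant effects, and its Implications section draws conclusions about EMA as a research instrument, as an intervention and as an ethical matter. A reader who believes the trial had 85% power at that line will take a non-significant result as good evidence that no relevant reactivity exists.

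**Working it through.** **Inputs.** From Sample size: k = 3 groups, m = 3 waves, r = .65, epsilon = .8, alpha = .05, power .85, d = 0.25, N = 120 (40 per group). From Analyses: baseline-adjusted model on T6 and T12, two-sided tests.

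**1. Reproducing the plan's figure.** For the repeated-measures within-between interaction:

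- λ = f²·N·m·ε/(1−r), df1 = (k−1)(m−1)ε, df2 = (N−k)(m−1)ε.
- With f = d/2 = 0.125 and N = 120: λ = 0.015625 × 120 × 3 × 0.8/0.35 = 12.86, df1 = 3.2, df2 = 187.2.
- Power = .851. At N = 119 it is .848, so 120 is exactly the smallest N.

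The other routes tried with three waves and 85% power do not give 120:

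| Variant | N |
|---|---|
| Interaction, f = 0.25 | 33 |
| Within factor, f = 0.125 | 99 |
| Between factor, f = 0.125 | 540 |
| Between factor, f = 0.25 | 138 |
| Interaction, f = 0.125, epsilon = 1 | 105 |
| Interaction, f = 0.118 (d√2/3) | 135 |
| SPSS or Cohen effect-size option, f = 0.25 | 129 to 132 |
| SPSS or Cohen effect-size option, f = 0.125 | 507 to 510 |

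**2. The interaction f that d = 0.25 really implies.** Let the groups be equal at T0, and let one or both EMA groups differ from control by d at T6 and T12.

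- Group pattern, centred: (2/3, −1/3, −1/3), up to sign. Mean square 2/9.
- Time pattern (0, 1, 1), centred: (−2/3, 1/3, 1/3). Mean square 2/9.
- f² = d² × (2/9) × (2/9), so f = 2d/9 = 0.0556.
- λ = 0.003086 × 120 × 3 × 0.8/0.35 = 2.54. Power = 22.6% at N = 120 and about 30% at N = 160.
- About 597 completers would be needed for 85%.
- Conversely, f = 0.125 corresponds to d = 0.125 × 9/2 = 0.56.

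**3. The planned baseline-adjusted comparison, one EMA group against control.** This step does not depend on which f was entered. In SD units:

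- Residual variance at one time point: 1 − .65² = .5775.
- Residual covariance of T6 and T12: .65 − .65² = .2275.
- Variance of their mean: (.5775 + .2275)/2 = .4025.
- SE with 40 per group: √(2 × variance/40).
- Detectable d at 85% power: (1.960 + 1.036) × SE. At the first Holm step for two comparisons (alpha .025): (2.241 + 1.036) × SE.

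| | Mean of T6 and T12 | One time point |
|---|---|---|
| SE | 0.142 | 0.170 |
| Power at d = 0.25, alpha .05 | 42% | 31% |
| Power at d = 0.25, alpha .025 | about 31% | about 22% |
| p if the observed d is exactly 0.25 | .08 | .14 |
| Detectable d, alpha .05 | 0.43 | 0.51 |
| Detectable d, alpha .025 | 0.47 | 0.56 |
| Completers per group for 85% at d = 0.25, alpha .05 | 116 | 166 |

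The table uses the normal approximation. With t distributions the 42% and 31% become 41.3% and 30.6%.

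**4. With the planned drop-out.** A simulation of 160 randomised, with 25% lost by T12 (stated) and 12.5% by T6 (assumed), gives 46% for the mean of both waves and 31% at T12.

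**The case against.** Four objections deserve an answer.

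- **The entry f = d/2 is inferred.** This is true: the article prints neither f nor the test. The match is exact on every printed input, but it is unique only among the variants tried. The conclusion does not need it, because step 3 uses only the stated N, r and alpha.
- **The 23% belongs to a test that is not the planned model.** With baseline as a covariate, the effect sits in the group terms rather than in a 3x3 interaction. This stands in part: 31% to 46% describes the planned analysis better. The 23% is what the protocol's own test family, which it calls essentially equivalent to the planned one, should have returned.
- **23% to 42% is not a hard bound.** This also stands. Interaction power is about 18% if the effect builds linearly to T12. More favourable readings raise it: 52% if both EMA arms are pooled against control (80 against 40), and the same if about 53 per arm all complete. In that full-retention case an observed averaged d of 0.25 would just pass .05 before Holm (0.25/0.123 = 2.03, p = .04), though not .025. If the two EMA arms move 0.25 SD in opposite directions, the interaction test has 61% at N = 120 and 75% at N = 160.
- **The protocol calls r = .65 conservative.** With r = .80, the averaged contrast has 58% with 40 per arm and 71% with 53 per arm all completing.

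None of these reaches 85%. The planned confidence intervals for d will show the real precision, which softens the risk of misreading but does not make the stated power correct.

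**Conclusion.** The concern holds. The claim of 85% power for d = 0.25 with 120 completers is wrong. On the protocol's own inputs, power is about 23% for the interaction test and about 31% (one time point) to 42% (mean of T6 and T12) for the planned comparison of an EMA group with control, before multiplicity correction. The difference that can be detected with 85% power is 0.43 to 0.51, roughly twice the stated target, and 0.47 to 0.56 at the first Holm step.

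These figures assume r = .65 between all waves, equal groups at baseline and a difference of 0.25 SD at the time points compared. That the error came from entering d/2 as the interaction f is a very likely explanation, but it is not documented. This must be corrected, because the trial's headline statement of sensitivity, and any reading of a null result, rests on it.

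**What to change.** Keep the recruitment target of 160 and restate what it delivers. Suggested text for Sample size: *With 40 completers per group and a correlation of .65, the baseline-adjusted comparison of each EMA group with control has 85% power for d of about 0.43 (mean of T6 and T12) or 0.51 (one time point) at a two-sided .05, and for about 0.47 or 0.56 at the first Holm step for two comparisons. For d = 0.25 the power before multiplicity correction is about 42% or 31%.*

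Then make three matching corrections:

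- In Sample size, remove the statement that a difference of 0.25 should reach significance, and the statement that 120 participants are enough for it.
- In the Abstract, correct the statement that the study is powered for a small effect.
- In the Discussion, correct the statement that the model can show effects beyond 0.25.

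The cost is wording only. No participants are added, and the design and model stay as they are. The price is a less favourable, but true, statement of what the trial can detect.
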